### **5.8. Masking**

The study will be double-masked. The primary and secondary outcome assessments will be performed by masked Investigators and the subject and parents/guardians will be masked to group allocation and study intervention until the data analysis is completed.

Masked Investigators will perform masked measurements of the primary and secondary efficacy outcomes (cycloplegic auto-refraction and axial length) at every 6-month visit. The masked Investigators will not be allowed to enter subjects' eye examination room and check their glasses, other than to perform their masked examination duties. Subjects will be told not to discuss their lens wear with the masked Investigator.

The children will be asked to wear the spectacles full-time. Compliance will be regularly monitored at every follow-up visit and through the completion of a questionnaire regarding their lens use.

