## 2. Study Plan Schematic

[figure not shown]

Remarks: At each 6-month visit, the criteria for updating the prescription of spectacle lenses for all groups include any of the following:

- Increase in myopia of 0.50D (spherical over-refraction) or more, in either one eye or both eyes
- Habitual visual acuity equal to or worse than 6/9.5, in either one eye or both eyes

An additional spectacle dispensing visit will be scheduled after a prescription update.

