## **5.6. Study intervention**

### **5.6.1. Phase 1: Two-arm RCT**

This study is a double-masked RCT. Subjects and parents are masked from the type of investigational lenses they are wearing. Masked Investigators will be responsible for masked measurements of the primary and secondary efficacy outcomes at the baseline and 6-monthly visits. Masked Investigators will never examine the subjects while they are wearing their spectacle lenses. Unmasked Investigators will conduct the remaining measurements and dispense the investigational lenses.

Eligible subjects will be randomly assigned to the control or the treatment group in an equal ratio. The control group will receive placebo SV lenses, while the treatment group will receive D2 lenses.

Scheduled visits will be conducted over a period of 2 years. The control group will cross over to wear D2 lenses at 12 months and all subjects will continue wearing D2 lenses for an additional 12 months.

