### **5.6.2. Phase 2: Auxiliary group**

To compare the efficacy and visual performance of D1 and D2 lenses for internal reference, an auxiliary group having the same number of subjects will be assigned to wear D1 lenses for 2 years. Recruitment criteria, measurement and follow-up intervals of the auxiliary group will be the same as in Phase 1 study.

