**5.15. Study visits time windows**

| Visit Number                    | Target Visit Window (days) | Acceptable Visit Window (days) |
|---------------------------------|----------------------------|--------------------------------|
| V1 (Baseline)                   | 0                          | 0                              |
| V2 (dispensing)                 | 30                         | 15-45                          |
| V3 (1-month after dispensing)   | 60                         | 53-67                          |
| V4 (6-month)                    | 180                        | 150-210                        |
| V5 (12-month)                   | 360                        | 330-390                        |
| V5a (dispensing)*               | 390                        | 375-405                        |
| V5b (1-month after dispensing)* | 420                        | 413-427                        |
| V6 (18-month)                   | 540                        | 510-570                        |
| V7 (24-month)                   | 720                        | 690-750                        |

\* Only applicable for control group

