### **8.6. Unmasking**

This is a double-masked trial, where both subjects and Investigators are masked to treatment allocation. Unmasking will only occur at the end of the study under the authorization of the project co-ordinator.

For individual emergency unmasking, where a related serious adverse event has occurred and the group allocation of the subject is required in order to enable clinical treatments to be planned, project co-ordinator will inform the allocation of the subject, and this will be documented. The masked Investigator will remain masked.

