## **10. Study completion**

All investigational spectacles (used or unused) will be returned to the research staff after completion of the final data collection visit. As a token of appreciation, each participant will receive either a pair of SV spectacles or MiyoSmart spectacles upon completion of the study.

As a double-masked RCT, subjects and parents/guardians are masked from the group allocation and study intervention until the data analysis is completed. After completion of study, they will receive a thank-you letter through email or WhatsApp

for participating in the study. The group allocation of subjects will also be disclosed in the thank-you letter.

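### The protocol promises families masking until data analysis, but the control-only V5b visit and 12-month lens switch let a family that knows the design infer original SV allocation in year 2

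*Protocol*

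**What the plan says.** Three places in the protocol make the masking promise, and none limits it to year 1. Section 5.8 says that "the subject and parents/guardians will be masked to group allocation and study intervention until the data analysis is completed". Section 10 says that "subjects and parents/guardians are masked from the group allocation and study intervention until the data analysis is completed". Section 8.6 says that "Unmasking will only occur at the end of the study under the authorization of the project co-ordinator", with an exception only for individual emergencies.

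The schedule treats the arms differently after month 12. Section 5.6.1: "The control group will cross over to wear D2 lenses at 12 months". The D2 arm stays on D2, and under Section 5.6.2 the auxiliary group "will be assigned to wear D1 lenses for 2 years". In the visit table of Section 5.15, V5a (dispensing, target day 390) and V5b (one month later, target day 420) carry the footnote "Only applicable for control group". Section 5.14 ties the month-13 choroidal scan and the second visual performance questionnaire to the control crossover. No matching visit is described for D1 or D2.

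Lenses may also be changed on indication in any arm. Section 2 lists the criteria for all groups, among them "Increase in myopia of 0.50D (spherical over-refraction) or more, in either one eye or both eyes", and adds: "An additional spectacle dispensing visit will be scheduled after a prescription update".

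**The concern.** A masking statement describes a property that the trial must actually have. If one arm alone has an extra visit with its own scan and questionnaire, plus a lens switch that needs no refractive indication, then the schedule itself carries allocation information. A family recalled for V5b can infer that the child wore SV in year 1 and now wears D2. A family not recalled can infer that the child has worn a DIMS lens throughout.

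Two kinds of year-2 data are exposed. The first is what families report. Wear time is collected at 18 and 24 months. The primary safety outcome in Section 1 is adverse events over 2 years, and Section 8.2.1 includes symptoms such as ghosting, glare and eye strain, whose reporting can depend on what the family believes about the lens. The second is SER and AL at V6 and V7, if the masked Investigator who measures them can see that a child had a V5b. Describing these data as double-masked would claim more than the design can assure.

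**Working it through.** The plan gives no figure for masking itself, and its sample-size figures play no part here. The check compares the passages and then does one piece of arithmetic on the visit table.

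1. **Scheduled visits by arm (Section 5.15).** Control: V1, V2, V3, V4, V5, V5a, V5b, V6, V7 = 9. D1 and D2: the same list without V5a and V5b = 7. After V5 this is 4 against 2.

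2. **Which difference is informative?**
   - A dispensing visit alone is not. Section 2 allows one in any arm after a prescription update. Section 5.16 heads the V2 and V5a column as also used on indication. Section 5.17.4 records lens updates, with no limit by arm, on the V2 and V5a forms. A D1 or D2 child may therefore have new lenses around month 12 and an entry on the V5a form.
   - A switch without a refractive indication is. It happens to every control child who does not meet the update criteria, and to no D1 or D2 child.
   - V5b is. Sections 5.14, 5.15 and 5.17.3 together give this visit, with its repeat scan and questionnaire, to the control group only.

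3. **When does it become informative?** V5b has target day 420 and an acceptable window of 413-427, and the last visit has target day 720.
   - At the target day: (720 - 420)/720 = 300/720 = 41.7%, about 42% of follow-up.
   - Over the window: (720 - 427)/720 = 40.7% to (720 - 413)/720 = 42.6%.

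4. **Can families draw the inference?** Section 7.2 requires that subjects and parents be fully informed about participation. The consent text is not available, so it is an assumption that they learn of the crossover and of who attends V5b.

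5. **Can masked Investigators?** Under Section 5.8 they measure cycloplegic autorefraction and AL at every 6-month visit, hence at V6 and V7. Section 6.3.1 restricts the participant's electronic folder to unmasked Investigators, but for REDCap it describes role-based limits only as something that can be arranged. Nothing says that the V5b form or the visit history is closed to the masked role.

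6. **What is untouched?** The primary and secondary outcomes (Sections 5.12 and 5.13) are changes to 12 months, measured at V5, before the crossover lenses are dispensed. D1 and D2 children have the same schedule, so V5b does not separate them.

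**The case against.** The strongest reply is that little depends on year 2. Both efficacy outcomes are fixed at 12 months, and Section 6.2 computes progression only from the baseline, 6-month and 1-year visits, so the protocol specifies no between-group efficacy test at 18 or 24 months. After crossover both Phase 1 arms wear D2. The post-crossover questionnaire is given only to controls, so it supports no concurrent between-arm comparison. Section 8.3 appears to assign the judgement of adverse event severity and relatedness to an unmasked Investigator and the PI, so V5b could change only what families report. All of this stands, and it limits the point to wear time, adverse event reporting and the assessor risk. It does not make the masking statement true.

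Several stronger readings are tempting, and the protocol does not support them:

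- *Only controls have a V5a form.* Sections 2, 5.16 and 5.17.4 allow dispensing and V5a entries in any arm.
- *Masked staff can see who attended V5b.* Access is not documented either way. It is an unclosed risk. Unmasked Investigators know allocation by design.
- *Masking is completely broken, or year 2 is simply open-label.* The family's inference depends on consent text that is not available, D1 against D2 stays masked, and assessor masking of SER and AL can be kept.
- *Universal lens renewal confounds year-2 efficacy.* A crossover from SV to D2 needs new lenses, and the protocol defines no year-2 efficacy estimate for the renewal to distort.

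**Conclusion.** The point holds in a limited form. Sections 5.8, 8.6 and 10 promise masking that the schedule cannot assure once V5b takes place. From about day 420 of 720, about 42% of follow-up, a family that knows the design can infer whether the original allocation was SV or DIMS. Year-2 wear time and the second year of the 2-year adverse event outcome are then collected with that allocation deducible, and assessor masking at V6 and V7 is not secured in writing.

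This rests on two assumptions: that families learn of the crossover and the control-only visit, as Section 7.2 suggests, and that no unseen procedure gives the other arms a matching visit. The 12-month primary and secondary outcomes do not depend on either. The statement should be corrected, but the trial's main comparison is not in doubt on this ground.

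**What to change.** 1. In Sections 5.8, 8.6 and 10, limit the participant-masking claim for SV versus DIMS allocation to the period through the V5 measurements.
2. State that year-2 participant-reported outcomes (wear time and adverse event reports) are collected with original SV allocation deducible, and that they are reported descriptively and not as double-masked.
3. State that the V5a and V5b forms and the visit history are closed to the masked Investigators' REDCap role, so that SER and AL at V6 and V7 remain assessor-masked. Section 6.3.1 already says that access can be limited by role.

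The cost is wording in three sections and one access setting, with no new visits and no change to the sample size or the 12-month analysis. The downside is a weaker masking claim for year 2, but an accurate one.

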### **5.9. Withdrawal criteria**

Subjects (or parents/guardians for subjects <18 years of age) are free to withdraw from participation in the study at any time upon request. No further data will be collected on subjects who withdraw from this study.

If significant intolerance to the treatment intervention is suspected at any time after randomisation, subjects can choose to withdraw or terminate treatment (either treatment or control group).

An Investigator may discontinue or withdraw a subject from the study for the following reasons:

- Significant study intervention noncompliance: unable to contact via 3 phone calls and 3 messages, more than 3 attempts to arrange missed follow-up appointments, wearing the spectacles less than 5 days a week and/or an average of less than 5 hours/day.
- If any clinical adverse event or situation occurs (e.g., allergies to eye drops, reduction of visual function such as diplopia, reduction of BCVA; subject to clinicians' judgement) such that continued participation in the study would not be in the best interest of the subject.

- If the participant meets an exclusion criterion (either newly developed or not previously recognized) that precludes further study participation.

Should subjects require discontinuation of treatment intervention for any reason, follow-up visits and data collection will not continue as scheduled. The reason for discontinuation or withdrawal from the study will be recorded on the Discontinuation/Withdrawal Case Report Form (CRF) in a web-based secure remote electronic database named Research Electronic Data Capture (REDCap). Subjects who signed the informed consent form and were Randomised but did not receive treatment intervention may be replaced. If there are subjects who signed the informed consent form, were Randomised, received the study intervention but were discontinued or withdrawn within the first month due to not meeting inclusion criteria (e.g., unable to tolerate spectacles or eye drops), and it is still within the recruitment period, then these participants' randomisation will be discarded and replaced with a participant from the next allocation. All spectacles (used or unused) will be returned to the unmasked Investigator upon withdrawal or discontinuation from the study.

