### **5.18. Protocol violations**

A deviation from the protocol when no amendment has been submitted and approved would be regarded as a protocol violation. All protocol violations must be documented and reported (recorded in electronic spreadsheets). The prescribed treatment dose is at least 10 hours of spectacle wear per day, 7 days a week (i.e., at least 70 hours each week). A subject is considered as compliant with the study protocol if he/she has worn the spectacles for at least 56 hours a week (7 days of at least 8 hours each). If the spectacle lenses are worn for less than 35 hours per week or for less than 3 days per week, it is defined as a protocol violation. A list of such subjects will be prepared prior to unmasking.

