### 6.2. Statistical analysis

Data from the right eyes will be used for analyses when both eyes show fast progression. If only one eye demonstrated fast progression, that specific eye would be used for analyses. Demographic and optometric data will be displayed as mean and standard deviation, or number and percentage as appropriate. The Chi-square test (or if appropriate, Fisher's Exact test) and unpaired t-test will be performed to compare baseline between-group differences in demographics (age, sex). Myopia progression will be calculated as the difference between SER and AL at the baseline, the 6-month and the 1-year visits, respectively.

The unpaired t-test will be used to compare the changes in primary and secondary outcomes between groups. The efficacy of myopia control of DIMS lens will be determined by dividing the difference in myopia progression (or axial elongation) between two groups with the myopia progression (or axial elongation) in the SV group, then multiplied by 100%. Multiple regression analysis will be employed to identify factors that may be associated with myopia control efficacy. Regarding visual performance and comfort, subjective ratings collected by questionnaires will be compared between groups using Mann-Whitney U test.

Treatment will be discontinued if any treatment-related adverse event arises, such as constant visual disturbance (e.g., ghosting, diplopia, glare, etc.). The number of subjects

discontinuing treatment prematurely for any reason will be summarised by reasons for discontinuation. The incidence of all serious adverse events will be summarised.

Data analysis will follow an intention-to-treat approach. Missing values of outcome variables and covariates will be replaced using multiple imputation procedures with 10 sets of imputations assuming missing at random. All analyses will be 2-tailed with a significance level of 2.5%.

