### **8.5. Documentation and follow-up**

At each study visit, the Investigator or designee will inquire about the occurrence of AEs/SAEs since the last visit. Any AE observed by the Investigator or reported by the subjects will be documented on an adverse event form onto REDCap as soon as possible after notification of the event. However, not all AEs require reporting, as they might not directly impact participant risk. Information to be collected includes event description, time of onset, clinician's assessment of severity, relationship to study product (assessed only by those with the training and authority to make a diagnosis), and time of resolution/stabilization of the event. All AEs occurring while on study must be documented appropriately regardless of relationship. All AEs will be followed to adequate resolution. An appointment will be arranged for 1-4 weeks following AE resolution to check for any recurrence or changes because of the AE. Changes in the severity of an AE will be documented to allow an assessment of the duration of the event at each level of severity to be performed. AEs characterized as intermittent require documentation of onset and duration of each episode. These will be followed-up and assessed by medically fit clinician. It will be left to the judgement of the research team to decide whether an AE is of sufficient severity to require discontinuing the participant from the study. A subject may also voluntarily withdraw from participating in the study due to what he or she perceives as an intolerable AE. If either of these occurs, the subject must undergo follow-up visits for trial assessment and be given appropriate care under medical supervision until symptoms cease, or the condition becomes stable.

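### Outcome collection ends when a child stops the study lens, so the intention-to-treat analysis rests on imputing these children from those still on their lens

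*Protocol*

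**What the plan says.** Protocol Section 5.9 sets the data-collection rule for a child who stops the lens: "Should subjects require discontinuation of treatment intervention for any reason, follow-up visits and data collection will not continue as scheduled". For a child who leaves the study it says: "No further data will be collected on subjects who withdraw from this study". The same section gives the investigator discretion to discontinue or withdraw a child for non-compliance, including "wearing the spectacles less than 5 days a week and/or an average of less than 5 hours/day", and has the spectacles handed back on withdrawal or discontinuation.

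Section 6.2 calls the analysis intention-to-treat and adds: "Missing values of outcome variables and covariates will be replaced using multiple imputation procedures with 10 sets of imputations assuming missing at random". The primary outcome (Section 5.12) is the change in spherical equivalent refraction (SER) from baseline to 12 months. The secondary outcome (Section 5.13) is the change in axial length (AL) over the same period.

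Three other passages bear on this:
- Section 8.5: after an adverse event leads to discontinuation or withdrawal, "the subject must undergo follow-up visits for trial assessment". The duty lasts only until the symptoms have gone or the condition has settled.
- Section 5.18 defines a protocol violation by a different wear limit: "If the spectacle lenses are worn for less than 35 hours per week or for less than 3 days per week".
- Section 6.2 also says "Treatment will be discontinued if any treatment-related adverse event arises", whereas Section 8.5 leaves discontinuing the participant to the research team's judgement and Section 5.9 says the investigator may act.

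**The concern.** An intention-to-treat estimate needs the 12-month outcome of every randomised child, including those who gave up the lens. Section 5.9 ends the scheduled measurement of exactly these children. Since the spectacles are returned, they are off the study lens, and every 12-month value that is observed comes from a child still followed on the assigned lens. Missing-at-random imputation within arm then gives a D2 child who stopped the outcome expected of a similar D2 child who continued.

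Two results are at stake: the difference in SER change, and the efficacy percentage in Section 6.2, which has that difference as its numerator. Both would describe the effect while the lens is worn, under a label that promises the effect of being assigned to it. Whether a measurement is taken is a protocol rule. A statistical analysis plan can choose how to impute, but it cannot recover a refraction that was never taken.

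**Working it through.** **The plan's own figures.** Inputs from Section 6.1: difference 0.315 D, SD 0.475 D, stated effect size 0.658, 90% power, two-sided. A two-sample t-test calculation at effect size 0.658 gives 49.5, so 50 per group at alpha 0.05, and 58.6, so 59 at alpha 0.025. Then 59 x 1.10 = 64.9, so 65. (0.315/0.475 is 0.663 and dividing by 0.90 gives 66; both differences are immaterial here.) The sample-size arithmetic is not at issue.

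**Size of the overstatement.** Two assumptions are needed that the protocol does not supply:
- f, the share of D2 children who stop the lens;
- L, the share of the 12-month benefit that these children lose.

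Also assumed: SV children who stop progress like other SV children, the SD is unchanged, and imputation is done within arm.

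Effect with everyone measured = 0.315 x (1 - f x L). 
Relative overstatement = 0.315 / [0.315 x (1 - f x L)] - 1.

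| f | L | Effect with all measured (D) | Overstatement (D) | Relative |
|---|---|---|---|---|
| 5% | 50% | 0.315 x 0.975 = 0.307 | 0.008 | 2.6% |
| 5% | 100% | 0.315 x 0.95 = 0.299 | 0.016 | 5.3% |
| 10% | 50% | 0.315 x 0.95 = 0.299 | 0.016 | 5.3% |
| 10% | 100% | 0.315 x 0.90 = 0.284 | 0.032 | 11.1% |
| 20% | 50% | 0.315 x 0.90 = 0.284 | 0.032 | 11.1% |
| 20% | 100% | 0.315 x 0.80 = 0.252 | 0.063 | 25.0% |

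**Check that missing-at-random imputation behaves this way.** A simulation used 65 per arm, 600 replicates, 10 imputations within arm, and a 6-month value correlated 0.7 with the 12-month value. It assumed 12-month SV progression of 0.6 D. Only on-lens 12-month outcomes were used for imputation.

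| f | L | Imputed estimate (D) | Estimate with all measured (D) |
|---|---|---|---|
| 10% | 50% | 0.314 | 0.298 |
| 10% | 100% | 0.312 | 0.280 |
| 20% | 50% | 0.317 | 0.283 |
| 20% | 100% | 0.310 | 0.246 |

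The imputed analysis returns essentially the full 0.315 D whatever the stoppers' true course.

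**Against the trial's precision.** The standard error of the difference at 59 per group is 0.475 x sqrt(2/59) = 0.087 D. An overstatement of 0.0315 D is therefore about 0.36 standard errors. If all 65 per group are measured, power at two-sided 0.025 is 90.6% to 87.0% for f = 10% (L = 50% to 100%) and 87.0% to 77.4% for f = 20%.

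**Wear limits side by side.** A child wearing the lens 4 days x 10 h = 40 h a week is under 5 days, so may be withdrawn under 5.9. That child is above both limits in 5.18, so is not a violator. A child wearing it 5 days x 6 h = 30 h a week is a violator under 5.18 but does not reach the 5.9 wear ground.

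**The case against.** The strongest case against has five parts.

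- **Section 8.5 might be read as the opposite rule to 5.9.** It is not. Its follow-up ends when the event resolves or stabilises, and it can be read as safety follow-up outside the visit schedule. The two sections are in tension and should be reconciled, but 8.5 neither reverses 5.9 nor secures the 12-month outcome.
- **A reader might infer that the loss is not at random because intolerance and poor wear trigger it.** That does not follow. Section 5.14 records wear at 1 month after dispensing and at 6 and 12 months. Loss that depends on recorded wear can be missing at random if wear enters the imputation model. Withdrawal for poor wear is discretionary, so some poor wearers will stay and supply outcomes. The argument is strong for children who stop completely and weaker for poor wearers.
- **The imputation model is not stated here.** Its covariates and any sensitivity analysis are ordinary content of a statistical analysis plan, so their absence is no defect of the protocol. What stands is that no imputation model can learn about off-lens outcomes that nobody measured.
- **The two wear limits serve different purposes.** One permits withdrawal, the other defines a listed violation. A child may meet one and not the other without logical contradiction, and neither limit drives the missing-data argument.
- **The planned 10% dropout is not all lens-stopping.** It also covers loss to follow-up and withdrawn consent (Sections 5.9 and 5.10), and children who stop late keep part of the benefit. A single figure of 11% at that rate is an upper end, not an expectation.

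**Conclusion.** The point holds in this form: Section 5.9 stops scheduled data collection when the lens is discontinued, Section 6.2 claims intention-to-treat with missing-at-random imputation, and no passage secures 12-month SER or AL after stopping. The resulting estimate is close to a while-on-lens effect.

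The overstatement of the 0.315 D difference runs from about 2.6% (f = 5%, L = 50%), through 5% to 11%, or 0.016 to 0.032 D (f = 10%, L = 50% to 100%), to 11% to 25% (f = 20%, same range of L). With the SV mean unchanged, the efficacy percentage is inflated by the same proportion. Both f and L are assumptions; a child who stops and takes up another myopia treatment could have a smaller L.

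A reader might go further and infer that the primary conclusion is unsafe. The figures do not support that: at 10% stopping the bias is at most about a third of a standard error and is unlikely alone to reverse the test. The reasons to act are that the label is wrong for the data collected and that unmeasured outcomes cannot be recovered later.

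**What to change.** Amend Section 5.9 so that stopping the lens and leaving the study are separate events. Suggested sense: children who stop the study lens, or wear it poorly, are still measured for SER and AL at the scheduled 6- and 12-month visits unless consent is withdrawn, and poor wear alone does not end data collection. This changes what is measured, not when treatment stops.

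Impute only outcomes truly missed. Add, in the protocol or the statistical analysis plan, a sensitivity analysis that departs from missing at random, for example one that gives D2 stoppers an SV-referenced course.

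The clinical team should reconcile:
- 5.9 with 8.5 on follow-up after an adverse event;
- 5.9 with 5.18 on wear limits;
- 6.2 with 5.9 and 8.5 on when treatment stops.

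No view is taken on which of these is right.

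**Cost.** A protocol amendment with ethics review and, if judged a substantial change under Section 12.2, a revised consent form and renewed consent from families already enrolled; then attendance at a few visits that are already scheduled. Loss to follow-up and withdrawn consent would not be recovered. With an anticipated start of August 2023, outcomes of children already discontinued may be beyond recovery.
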